## Abstract

This clinical trial (ChiCTR1800019185) is designed to be an open‐label, prospective, single‐center, single arm exploratory research study. The study will recruit non‐small cell lung cancer patients (NSCLC) with slow progression after first‐line treatment with EGFR‐TKI drugs. Slow progression will be confirmed by the presence of serum carcinoembryonic antigen or imaging evaluation. The primary aim is to assess progression‐free survival after EGFR‐TKIs treatment combined with apatinib 250 mg once daily. The secondary objectives are to evaluate objective efficacy, disease control rates, quality of life, overall survival, and safety. From September 2018 to September 2020, under specific entry and discharge standards, we plan to enroll 38 eligible patients until the end of the study. We hope that our study will help to explore a new way of combining the small molecular inhibitors of antiangiogenesis with EGFR‐TKIs to overcome acquired drug resistance.

## Introduction

Lung cancer is the most common malignant tumor worldwide. Non‐small cell lung cancer (NSCLC) accounts for 80% of lung cancers.^1^ In Chinese males, lung cancer is the most common tumor type and has the highest mortality rates. In Chinese females, lung cancer is the second most common tumor type, and has the highest mortality rates. According to the United States Surveillance, Epidemiology, and End Results database, 57% of lung cancer patients have distant metastases at the time of initial diagnosis.^2^ Therefore, the treatment of advanced patients is an important part of lung cancer treatment. Nonsquamous cell NSCLC accounts for approximately 70% of NSCLC. If not treated promptly, it will spread to other organs of the body, causing serious complications. EGFR‐TKI has been approved for the first‐line treatment of advanced NSCLC patients with EGFR‐positive mutations.^3^ However, some patients develop drug resistance after using EGFR‐TKI drugs. In most cases, this is due to a point mutation in position 790 of EGFR 20 exon, one of the most recognized drug resistance mechanisms.^4^ There are two manifestations of drug resistance in clinical practice, slow progression and explosive progression. According to the response evaluation criteria in solid tumors (RECIST) 1.1 tumor staging criteria, the clinical manifestation of patients with slow progression is between stable disease (SD) and progressive disease (PD). Tumor diameter and relative increases of 0%–20% is one of the criteria for slow progression. In slow progression NSCLC, there is no clear standard of care, and EGFR‐TKI can be considered in combination with antiangiogenic drugs.

Angiogenesis is a key step in the development and progression of malignant tumors.^5^ It is generally believed that angiogenesis in the tumor area provides nutrients and entraps metabolites, allowing tumor cells to be transferred to other parts of the body through new blood vessels. Therefore, effective inhibition of angiogenesis in tumor areas can inhibit the growth of tumor cells while reducing the occurrence of metastasis. At present, antitumor angiogenesis has become a promising new strategy for cancer treatment. The development of tumor neovascularization is associated with a variety of vascular‐related factors. Rapidly growing tumor cells can secrete multiple vascular growth factors under hypoxia, stimulating tumor angiogenesis. One of the most important growth factors is vascular endothelial growth factor (VEGF). VEGF binds to the VEGF receptor (VEGFR), stimulates VEGFR‐mediated downstream signaling, and ultimately leads to tumor angiogenesis.^6^ It is thought that VEGFR and human epidermal growth factor receptor 1 (HER‐1)/epidermal growth factor receptor (EGFR) share a common downstream signaling pathway, so EGFR‐TKI can also downregulate VEGF. Studies have shown that VEGF inhibitors can also inhibit HER‐1/EGFR signaling. VEGFR‐2 is a major mediator of endothelial cell function in VEGF. When endothelial cells are stimulated by VEGF, VEGFR‐2 promotes cell proliferation mainly through the PKC/RAF/MAP pathway and modifies or activates various signaling molecules. These include Akt, ERK‐2, PI3K, FAK, and Caspase‐9. Activation of Akt/PI3K can promote the downstream signaling cascade of EGFR, and there is cross‐reactivity between the two pathways. Theoretically, the combination of the two has at least an additive effect.

Carcinoembryonic antigen (CEA) is an acidic glycoprotein with the characteristics of human embryonic antigen. It exists on the surface of cancer cells differentiated from endoderm cells and is the most widely used broadspectrum tumor marker in clinical practice. CEA is present in 40%–80% of lung cancers, and is associated with tumor metastasis and recurrence. As such, it is of prognostic significance.^7^ Dynamic monitoring of CEA levels to reflect efficacy has been recognized. Multiple studies have found that CEA levels in PD patients are higher than before treatment. As such, we will use imaging to determine the sum of the diameters of all measured target lesions throughout the experiment, and this will be used as a reference point. Screening criteria for enrolling patients will include RECIST tumor staging criteria, screening patients with tumor diameters and relative increases of 0%–20% after previous EGFR‐TKI monotherapy, and increased CEA levels after previous EGFR‐TKI monotherapy.^8^

Previous studies have shown that EGFR‐TKI combined with an antiangiogenic drug (bevacizumab) is effective in the treatment of advanced NSCLC, and can improve patient survival.^9^, ^10^, ^11^, ^12^ The clinical study of bevacizumab combined with erlotinib in EGFR‐TKI resistance has also made breakthroughs. In the BELIEF study published at the 2015 European Cancer Congress, patients with advanced nonsquamous NSCLC and EGFR exon 19 deletion or exon 21 (L858R) mutation were enrolled. The study investigated the effects of erlotinib plus bevacizumab treatment on PFS in patients with or without EGFR T790M mutation.^13^ Preliminary results indicated that all patients, T790M‐positive patients, and T790M‐negative patients showed progression‐free survival (PFS) of 13.8, 16.0, and 10.5 months, respectively, which appeared to indicate that antiangiogenic drugs plus EGFR‐TKI were suitable for patients with T790M mutations. The results need to be further explored.

Apatinib is a small molecule VEGFR tyrosine kinase inhibitor (TKI) developed by Hengrui Pharmaceutical Co., Ltd. with independent intellectual property rights. The drug mainly inhibits VEGFR‐2 to exert antiangiogenic effects to treat malignant tumors. in vitro and in vivo tests have shown that apatinib has good antitumor activity against lung cancer. In a phase 2 randomized, double‐blind, placebo‐controlled trial, this product was observed as a third‐line treatment for patients with advanced nonsquamous NSCLC. Compared with the placebo group, median progression‐free survival (mPFS) was prolonged by 2.8 months.^14^ Phase 3 clinical trials are still ongoing.

In summary, angiogenesis inhibitors combined with EGFR‐TKI can significantly improve the efficacy of EGFR‐TKI in EGFR‐positive patients, delaying the occurrence of drug resistance. T790M‐positive disease is the main indication for TKI treatment of NSCLC resistance, followed by slow progression. Ideal initial data would suggest that antiangiogenic drugs plus EGFR‐TKI treatment of T790M‐positive patients have certain clinical significance.

This study will investigate the efficacy and safety of continuous EGFR‐TKI and apatinib (angiogenesis inhibitor) treatment in patients with NSCLC determined to have slow progression by CEA or imaging after first‐line treatment with EGFR‐TKI (including erlotinib, gefitinib, and icotinib). In addition, the study will analyze the correlation between clinical characteristics (EGFR gene mutation status, gender, staging, etc) and therapeutic efficacy. The study design flow is shown in Figure 1.

**Figure 1 tca13303-fig-0001:**
[figure not shown]
The study design flow.

### Primary endpoint

PFS: the time from randomization to patients experiencing tumor progression or death.

### Secondary endpoints

Overall survival (OS): time from randomization to death from any cause.Objective response rate (ORR): refers to the proportion of patients whose tumor shrinkage has reached a certain level and maintained for a certain period of time, including cases of complete response (CR) and partial response (PR). RECIST 1.1 criteria were used to evaluate objective tumor remission. The patients must have measurable tumor lesions at baseline. According to RECIST 1.1, the evaluation criteria of efficacy can be divided into CR, PR, SD and PD.Disease control rate (DCR): refers to the percentage of patients with confirmed CR, PR and disease stability (≥4 weeks) in the patients with evaluable efficacy.Quality of life score (QoL), refers to the EORTC QLQ‐C30 (version 3, Chinese version) evaluation method. The questionnaire evaluates changes in clinical symptoms and objective examination results of tumor patients before and after treatment. The results of each field of the QoL scale will be recorded in the electronic case report form (eCRF).Drug safety: patients will be monitored for adverse events occurring during the period of clinical research. In addition, patients will undergo clinical laboratory tests, and clinical characteristics will be monitored, including severity, occurrence time, duration, treatment and prognosis. Any correlation between experimental drugs will be documented. Common Terminology Criteria for Adverse Events (CTCAE) version 4.0 will be used to categorize adverse events.

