#### Criteria for excluding patients from analysis

Study drugs were not taken in accordance with the protocol, making it impossible to evaluate efficacy and/or safety.

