### During treatment (every four weeks for a cycle, every two cycles for the efficacy evaluation)

#### Singular period

Patients will undergo the following evaluations: vital signs, physical examination, blood pressure, coagulation function, ECG, ECOG PS score, routine blood tests, routine urine tests, routine stool tests, liver and kidney function, electrolyte, tumor markers, biomarkers, CEA, QoL score, adverse events, and concomitant medication.

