#### Full analysis set

This will be comprised of all patients who receive at least one dose of the study drug. Data from the last observation carried forward (LOCF) will be used in cases where the full course of treatment was not observed.

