#### Safety analysis set

This will be comprised of all patients who receive at least one dose of study drug and have any safety information recorded. This data set will be used for security analysis.

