### Statistical analysis plan

All statistical analysis will be performed by SPSS 19 statistical analysis software. All statistical tests will be performed by bilateral test. *P*‐values ≤0.05 will be considered statistically significant, and the 95% confidence interval reliable.

Baseline data will be analyzed according to the full analysis set, and all efficacy indicators will be analyzed according to the full analysis set and the per protocol set. Security analysis will be performed using the safety analysis set.

Abscission analysis: descriptive analysis will be used to compare of total abscission rate. Abscission rate due to adverse events will be performed using a chi‐square test or Fisher's exact probability test.

Efficacy analysis: for indicators PFS and OS, the product limit method will be adopted and 25%, 50% (median), 75% PFS and OS at different times after treatment will be calculated, respectively according to the actual situation of the data.

Safety analysis: descriptive statistics will be used to describe the adverse events in this study. Laboratory test results will be summarized using descriptive statistics.

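### The disease control rate is defined on evaluable patients only, against the plan's own full analysis set, and an exclusion rule for analysis names no set

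*Protocol article*

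**What the plan says.** All places are in the protocol article.

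- **Secondary endpoints.** DCR "refers to the percentage of patients with confirmed CR, PR and disease stability (≥4 weeks) in the patients with evaluable efficacy". The objective response rate (ORR) in the same section carries no such restriction to evaluable patients.
- **Full analysis set.** It holds "all patients who receive at least one dose of the study drug". Last observation carried forward (LOCF) "will be used in cases where the full course of treatment was not observed".
- **Statistical analysis plan.** Here "all efficacy indicators will be analyzed according to the full analysis set and the per protocol set", and safety is analysed on the safety analysis set.
- **Safety analysis set.** It holds "all patients who receive at least one dose of study drug and have any safety information recorded".
- **Criteria for excluding patients from analysis.** The ground given is: "Study drugs were not taken in accordance with the protocol, making it impossible to evaluate efficacy and/or safety". No analysis set is named.
- **During treatment.** The schedule is "every four weeks for a cycle, every two cycles for the efficacy evaluation".
- **Overall study design** lists toxicity or intolerance, withdrawn consent and investigator judgement as reasons to leave the study. The **After treatment** visit lists adverse events, concomitant medication and quality of life, but no imaging.

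**The concern.** The article fixes two incompatible denominators for one endpoint. A dosed patient without a usable tumour assessment belongs to the FAS but not to the group in which DCR is defined. Such patients are not a random subset, because toxicity, deterioration and early death are the likely reasons for having no scan. In a single-arm, open-label study no comparator would share the distortion, and a choice of denominator made after the data are known would be open to question.

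The exclusion criteria add a second conflict. As worded, they could take a dosed patient out of any analysis, including safety, on a judgement that evaluation was impossible. The FAS and safety set definitions keep such a patient, the safety set on condition that some safety information was recorded.

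**Working it through.** **Inputs.** N = 38 is the planned enrolment (Abstract: "we plan to enroll 38 eligible patients until the end of the study"), and I assume that all 38 are dosed. The article gives no expected DCR, no non-evaluable rate and no adverse-event rate. There is therefore no figure of the plan's own to reproduce, and every count below other than 38 is assumed.

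**Step 1: when the first assessment falls.** 2 cycles × 4 weeks = 8 weeks. A patient who leaves before week 8 has no scheduled post-baseline tumour assessment, and the listed after-treatment visit does not supply one.

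**Step 2: the two denominators.** Let x be the number of patients with documented control and m the number of dosed patients who are not evaluable.

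- All dosed, unassessed counted as not controlled: x/N
- Evaluable only: x/(N − m)
- Difference: x·m / [N(N − m)], which is never negative

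For x = 28 and m = 4: 28/38 = 73.7%, 28/34 = 82.4%, and the difference is 112/1292 = 8.7 points. For m = 6: 28/32 = 87.5%, a difference of 13.8 points.

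| Controlled (x) | All dosed, x/38 | m = 2 | m = 4 | m = 6 | m = 8 |
|---|---|---|---|---|---|
| 19 | 50.0% | 52.8% | 55.9% | 59.4% | 63.3% |
| 23 | 60.5% | 63.9% | 67.6% | 71.9% | 76.7% |
| 27 | 71.1% | 75.0% | 79.4% | 84.4% | 90.0% |
| 30 | 78.9% | 83.3% | 88.2% | 93.8% | 100.0% |

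With four non-evaluable patients, the gap runs from 5.9 points (x = 19) to 9.3 points (x = 30). For scale, the exact 95% confidence interval for 23/38 is 43.4% to 76.0%.

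**Step 3: does LOCF reconcile them?** A patient without a post-baseline scan has no later value to carry. If the baseline were carried instead, the recorded change would be zero, which reads as stable disease. Crediting all four such patients would give (28 + 4)/38 = 32/38 = 84.2%, above even the evaluable-only 82.4%. The same data could thus be reported as 73.7%, 82.4% or 84.2%, depending on which sentence is followed.

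**Step 4: the exclusion criteria and safety.** Suppose 12 of 38 patients (31.6%) have a given adverse event and four patients are removed, of whom k had it. The rate becomes (12 − k)/34: 35.3%, 32.4%, 29.4%, 26.5% or 23.5% for k = 0 to 4. The break-even is k = 4 × 12/38 = 1.26, so the rate rises for k = 0 or 1 and falls for k of 2 or more.

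**Step 5: the 4-week minimum for stable disease.** A patient stable at the first scheduled scan already has about 8 weeks of follow-up, so the minimum removes nobody there. It matters only for an unscheduled scan between weeks 4 and 8. As an outer bound, suppose every patient were credited at week 4, with exponential progression-free survival and 4.345 weeks to the month. For an assumed 4-month median, 85.3% are progression-free at week 4 and 72.7% at week 8, a gap of 12.6 points. For a 13.8-month median the figures are 95.5% and 91.2%, a gap of 4.3 points.

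**The case against.** **Detail left to another document.** Handling of missing scans is often left to a full protocol or analysis plan, and neither is shown. That would answer a complaint of silence. It does not answer this one, because the article itself states both denominators and applies the FAS to every efficacy measure.

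**The exclusion criteria may be a per-protocol rule.** They apply only where evaluation was impossible, and the analysis section assigns safety to its own set. This is a fair reading and may be what was meant. The text does not say so, however, and it mentions safety, for which the per protocol set is not used. The passages need reconciling; they do not prove that dosed patients will be dropped from safety.

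**Three stronger readings are tempting, and the article does not support them.**

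- A reader might infer that the exclusions make safety look better than it is. Step 4 shows that the rate can move either way. A patient with a recorded severe event has safety information and meets the safety set definition, and stopping for toxicity is a listed reason for withdrawal, so it is not in itself a failure to follow the protocol.
- A reader might infer that the 4-week minimum inflates DCR. At scheduled scans it is non-binding, and no unscheduled early scan is planned.
- A reader might infer that DCR cannot show activity because entry selects tumours that grew by 0% to 20%. The inclusion criteria also admit certain limited progressive disease and rising carcinoembryonic antigen, and the interval over which the growth occurred is not given. Any projected growth would rest on an assumed interval.

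**The true status of unassessed patients is unknown.** This stands. Counting them as not controlled is a conservative convention, and the statement that the evaluable-only rate is never lower depends on it.

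**Conclusion.** The concern holds for the denominator and for the unnamed analysis set. The definition of DCR contradicts the FAS definition and the rule that applies the FAS to all efficacy measures. Following the definition can only raise DCR relative to all dosed patients with unassessed patients counted as not controlled. With 38 patients and four non-evaluable, the increase is about 6 to 9 points over the range examined (19 to 30 controlled). Its actual size depends on counts that the article does not give.

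The exclusion criteria conflict with the FAS and safety set definitions until they name a set, and no direction of effect on adverse-event rates is established. The mismatch between the 4-week minimum and the 8-week schedule is a minor alignment point. DCR is a secondary endpoint and the remedy is wording, so this should be corrected but does not threaten the primary analysis of progression-free survival.

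**What to change.** 1. Compute DCR and ORR over the FAS. Count dosed patients without a post-baseline tumour assessment as not controlled and as non-responders, and state that LOCF is not used for these endpoints. Report the evaluable-only rate as a sensitivity analysis, with the number of non-evaluable patients and the reasons.
2. State that the criteria for excluding patients from analysis apply to the per protocol set only, and remove no patient from the FAS or the safety analysis set as those are defined.
3. As a minor alignment, tie the minimum duration of stable disease to the first scheduled assessment at week 8, with a visit window.

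The cost is a change of wording, with no extra patients or visits. DCR and ORR become somewhat lower, and some patients counted as not controlled may in truth have been stable; the sensitivity analysis shows how much that matters.

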### Statistical analysis of data

#### Data sets

There will be three sets of analyses in this study as follows.

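### The disease control rate is divided by an undefined group of evaluable patients that is none of the three analysis sets, and it can be overstated if treated patients without a tumour evaluation are left out

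*Protocol article*

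**What the plan says.** The Secondary endpoints section defines DCR by its denominator as well as its numerator: it "refers to the percentage of patients with confirmed CR, PR and disease stability (≥4 weeks) in the patients with evaluable efficacy". ORR, defined just before it, "refers to the proportion of patients whose tumor shrinkage has reached a certain level", with no evaluability limit on the patients counted.

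The Data sets section states: "There will be three sets of analyses in this study as follows". The sets are the full analysis set, the per protocol set and the safety analysis set. On the full analysis set the article says: "This will be comprised of all patients who receive at least one dose of the study drug", and then: "Data from the last observation carried forward (LOCF) will be used in cases where the full course of treatment was not observed". The Statistical analysis plan section adds that "all efficacy indicators will be analyzed according to the full analysis set and the per protocol set".

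The heading of the treatment-period visits gives the schedule: "every four weeks for a cycle, every two cycles for the efficacy evaluation". The Overall study design section lists toxicity or intolerance, withdrawal of consent and investigator judgment as reasons for leaving the study.

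**The concern.** The article gives two different populations for the same endpoint. A treated patient with no tumour evaluation belongs to the full analysis set, but on the ordinary meaning of the words is outside the DCR denominator.

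Who is evaluable is likely to depend on outcome. Patients who die or stop for toxicity in the first weeks are the least likely to have a scan at about week 8, so the patients removed would tend to be failures. The trial has a single arm, so no comparator carries the same bias, and any overstatement goes straight into the reported rate. If ORR is computed over all treated patients and DCR only over evaluable ones, DCR minus ORR is no longer the share with stable disease.

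**Working it through.** **1. The rules side by side.**

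| Section | Population for DCR | Treated patient with no evaluation |
|---|---|---|
| Secondary endpoints | patients with evaluable efficacy, undefined | left out, on the ordinary meaning |
| Full analysis set, with Statistical analysis plan | everyone with at least one dose | in the denominator; LOCF may supply a value |
| Per protocol set, with Statistical analysis plan | compliant patients with complete eCRFs | no missing data filled in |

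**2. Inputs.** The planned sample is N = 38 (Abstract). Cycles last four weeks and efficacy is evaluated every two cycles, so the first scheduled evaluation falls at 2 × 4 = 8 weeks. The article gives no expected DCR and no early-loss rate, so there is no figure of its own to reproduce. Assumed: all 38 are dosed; k of them are not evaluable; the evaluable DCR is 60–80%.

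**3. Formulas.** With x patients controlled:

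- evaluable-only DCR = x/(38 − k)
- DCR with unevaluated patients counted as not controlled = x/38
- ratio of the two = 38/(38 − k)
- difference = evaluable DCR × k/38

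**4. Results over the assumed range.**

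| k | Ratio 38/(38 − k) | Evaluable-only, near 70% | Over all 38 | Difference | Difference at about 60–80% |
|---|---|---|---|---|---|
| 0 | 1.00 | 27/38 = 71.1% | 27/38 = 71.1% | 0 | 0 |
| 2 | 1.06 | 25/36 = 69.4% | 25/38 = 65.8% | 3.7 points | 3–4 points |
| 4 | 1.12 | 24/34 = 70.6% | 24/38 = 63.2% | 7.4 points | 6–8 points |
| 6 | 1.19 | 22/32 = 68.8% | 22/38 = 57.9% | 10.9 points | 9–13 points |
| 8 | 1.27 | 21/30 = 70.0% | 21/38 = 55.3% | 14.7 points | 13–17 points |

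At k = 4 the exact (Clopper-Pearson) 95% intervals are 52.5–84.9% for 24/34 and 46.0–78.2% for 24/38.

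**5. The effect of LOCF.** If the full analysis set rule carried a baseline state forward as stable disease, the k unevaluated patients would be added to the numerator. At k = 4 that gives (24 + 4)/38 = 28/38 = 73.7%. The same data would then give 63.2%, 70.6% or 73.7%, depending on which rule is followed.

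**The case against.** A reader might infer that early deaths and toxicity stops are certain to disappear from DCR. The article does not establish that. Evaluable efficacy is undefined, and an early death could be classed as an evaluable failure. The one place that says when efficacy cannot be evaluated, the section on excluding patients from analysis, ties it to drug intake: "Study drugs were not taken in accordance with the protocol, making it impossible to evaluate efficacy and/or safety". The term could also mean only that lesions were measurable at baseline, which the inclusion criteria already require; every eligible patient would then be evaluable. Imaging before week 8 is not ruled out, and a patient who progressed on such a scan would count as evaluable.

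A reader might also infer that the two rules cannot both be followed, or that DCR is inflated relative to the plan's own full analysis set. Neither is shown. Evaluability can be read as a condition applied within that set. With LOCF, the full analysis set rate might even exceed the evaluable-only rate, as in step 5. The overstatement is therefore measured against counting unevaluated patients as not controlled, a rule that the article does not state.

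The sizes rest on an assumed k. The larger rows need 6 or 8 of 38 patients unevaluated, and the entry criteria (slow progression, low symptom score, expected survival of at least 12 weeks) select against early loss. At k = 2 the shift is small beside the sampling error. The ORR contrast is partly an argument from silence, because no ORR denominator is spelled out.

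All of that stands as a limit on the claim. It does not remove the point. This is not detail left to an unseen analysis plan: the article itself states a denominator for DCR and a different population for all efficacy indicators, and no section says that unevaluated patients count as not controlled.

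**Conclusion.** The point holds in a limited form. The stated DCR denominator is undefined, matches none of the three analysis sets, and differs from the population assigned to all efficacy indicators. On its ordinary meaning it can overstate DCR, compared with counting unevaluated treated patients as not controlled, by a factor of 38/(38 − k): about 3–4 points for k = 2 and 6–8 points for k = 4. This assumes that all 38 are dosed and that the evaluable DCR is 60–80%. The direction is certain as soon as one treated patient is left out; the size cannot be taken from the article, and it is nil if everyone is evaluated.

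DCR is one of several secondary endpoints in an exploratory trial, and the PFS analysis does not depend on it. The definition should still be settled before the data are analysed, since a few patients move the rate by several points.

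**What to change.** - In Secondary endpoints, define the denominator of both ORR and DCR as the full analysis set. Count a patient with no post-baseline tumour evaluation as not responding and not controlled, and report exact 95% confidence intervals.
- In Full analysis set, state that LOCF does not apply to ORR or DCR. Without this, a baseline state carried forward could count as stable disease, and naming the set alone would not remove the problem.
- Keep the evaluable-only DCR, if wanted, as a labelled supplementary figure, with a definition of evaluable and the number of patients not evaluable and the reasons.

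The cost is a sentence in each of two sections and possibly a somewhat lower reported DCR. Sample size, visits, data collection and the primary PFS analysis stay as they are.
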